## Methods/design

### Study design

The Patient Teaching Associate (PTA) Feedback Study is designed as a randomized, controlled, assessor- and patient-blinded, single-centre exploratory trial with two parallel groups after six student consultation sessions (Figure 1). The CONSORT statement has been used as the framework for the methodology of this study.

**Figure 1 Fig1:**
[figure not shown]
**Flow chart of the proposed Patient Teaching Associate (PTA) feedback study.** PTA, patient teaching associate.

### Setting and participants

The trial will be conducted from March 2013 to March 2014 at Monash University Eastern Health Clinical School, Victoria, Australia. The setting of the teaching programme is an after-hours general practitioner clinic that is adapted as a medical student teaching clinic during the day. The programme recruits real patients with chronic illnesses from the community, and aims to promote a patient-centred approach to consultation [12]. Clinical tutors are senior medical practitioners, including general practitioners, physicians and surgeons.

Sixty-six medical students in their first clinical year will be recruited to this study. Participants eligible for the trial are third-year students enrolled in Monash University and Deakin University attending Eastern Health Clinical School and willing to participate in the teaching programme. Students will see the same patients in groups of three. There are no exclusion criteria. Written consent will be obtained from all participants.

### Interventions

Eligible students will be randomized in equal proportions to receive either patient satisfaction score feedback with usual verbal multisource feedback or usual verbal multisource feedback alone, as control.

Students in both the intervention and control group receive oral feedback from the tutor, PTA and peers immediately following each patient consultation. Both intervention and control groups receive immediate oral feedback according to the Rating Instrument of Clinical Consulting Skills (RICS) framework [13].

The educational intervention is written feedback using the 21-item Medical Interview Satisfaction Scale (MISS-21) in addition to the usual oral feedback [14]. The MISS-21 is a widely available 21-item validated visit-based questionnaire for measuring patient satisfaction in the primary care context. The MISS-21 questionnaire can be found in appendix 1 of the article by Meakin *et al.*
[14]. Students in the intervention group will receive their intervention pack no later than one week prior to the last consultation during one semester (generally six consultations in total). The intervention pack includes patient feedback questionnaires for all previous student-led consultations as well as written instructions about self-reflection on the feedback received based on the Pendleton feedback framework [15].

### Primary outcome measure

The primary outcome measure is patient satisfaction immediately after the student consultation episodes, rated using the MISS-21 [14]. The consultation satisfaction questionnaire has been used to rate general practitioners and nurse practitioners. It is chosen because of its ease of administration, as it is visit-based and free from cost- or facility-based questions, has reported validity and reliability, and is a commonly used feedback tool in the consultation based clinical setting [16–18]. An independent researcher interviews each PTA after each consultation to obtain the scores.

### Secondary outcome measures

The RICS is the secondary outcome measure. The performance score by tutors gives a composite score and subscale scores of patient-centred approach, history taking, physical examination and problem solving and management. Tutors receive standardization training based on a video and complete the assessments within 24 hours of the student consultation episodes. The RICS was chosen because it is a student performance assessment tool designed for the Patient Partnership Program, a similar teaching programme developed at the Launceston Clinical School, University of Tasmania [19, 20]. Its construct validity and psychometric properties have been reported [13]. The concurrent use of the RICS avoids the risk of a simple training effect on MISS-21 scores.

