### Sample size

In the power calculation, we used the unpaired *t* test to detect a difference in the primary outcome (MISS-21) between the two groups. The RICS score, as the secondary outcome measure, was not used in the power calculation.

We incorporated the standard deviation in a nurse practitioner group in a trial using MISS-21 measurement [21]. There is, to date, no student data on MISS-21, and nurse practitioners are therefore chosen as the most likely comparator group. The medical student participants, in their first clinical year, are more likely still to be using a â€˜script-based’ clinical consultation style with less variability and are not considered comparable to experienced doctors. With 33 participants per group, there is 80% power of detecting a difference of at least 0.32 points in the MISS-21 at 5% significance level, assuming the standard deviation in the control group is 0.46 [21]. Cohen’s *d* = 0.69 indicates that a difference of 0.32 points has a moderate to large effect size in the primary outcome.

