### Allocation concealment and blinding

Allocation numbers are kept in sealed containers. Tutor and patient assessors will be blinded to group membership. Emergency unblinding will be considered only on student participants’ request and approval. For example, a student may experience significant distress and request tutor counselling or debriefing after receiving written feedback.

Tutor assessors, patient assessors and data analysts are blinded to group assignment of participants. Because of the nature of the feedback, student participants will not be blinded to the group membership.

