### Data management and statistical methods

All data will be entered electronically. The dataset will be recorded in a spreadsheet maintained on a secured University server. All forms related to the study will be kept in locked cabinets. Access to the study forms and electronic data will be restricted. All reports will be prepared such that no individual participant can be identified.

All data will be analyzed using SPSS (IBM Corp. Armonk, NY, USA.) and Stata (StataCorp LP, College Station TX, USA). We will compare student characteristics between the two groups using a chi-squared test for categorical variables and a *t* test for continuous variables. We will model data using regression analysis to assess any change in mean score on the MISS-21 and RICS patient-centeredness subscale (dependent variables) at the first and last tutorial session for both groups and to determine whether any differences exist between intervention and control groups (independent variables), taking the following covariates into account: age, sex, education in years, postgraduate status and international student status. They may enter the regression model only if the covariates are imbalanced between the two groups after randomization due to chance.

Additional subgroup analyses will be performed for the following variables: undergraduate versus postgraduate study, work experience, local versus international students status and language spoken at home.

There will be no control group for patient assessors. We will use linear mixed effects regression to account for random effects of variability in student grouping and variability in patient characteristics.

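### Tutors may score the RICS after hearing the patient's opinion, so its use as a guard against a MISS-21 training effect is unprotected

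*Protocol article*

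**What the plan says.** All references are to the protocol article.

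- **Interventions.** Students in both arms "receive oral feedback from the tutor, PTA and peers immediately following each patient consultation". Both arms also "receive immediate oral feedback according to the Rating Instrument of Clinical Consulting Skills (RICS) framework". The oral round is therefore built on the instrument that tutors later score.
- **Secondary outcome measures.** Tutors "complete the assessments within 24 hours of the student consultation episodes". The section closes with the purpose of having a second measure: "The concurrent use of the RICS avoids the risk of a simple training effect on MISS-21 scores".
- **Primary outcome measure.** The MISS-21 is collected separately: "An independent researcher interviews each PTA after each consultation to obtain the scores". No comparable separation is described for the tutor's score.
- **Allocation concealment and blinding.** "Tutor and patient assessors will be blinded to group membership". This covers the arm, not what the patient thought of the consultation.
- **Data management and statistical methods.** The regression takes two dependent variables, the MISS-21 and the patient-centredness subscale of the RICS.

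**The concern.** The article gives the RICS a specific job. Students in the intervention arm see completed MISS-21 forms before their last session and could learn what the questionnaire rewards. Their MISS-21 scores might then rise without better consulting. The RICS is meant to show whether that has happened, which it can do only if the tutor's score does not take in the patient's opinion.

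The stated timing leaves that open. The oral round starts at once and the scoring window runs for a day, so a tutor may fill in the form after hearing the patient and peers comment on the same domains. Blinding to arm does not help, because what is passed on is the patient's satisfaction and not the allocation.

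At stake is how a positive RICS result is read. In the very case the RICS is there to detect, more satisfied patients in the intervention arm can say so in front of the tutor, and the RICS can move as well. An echo of the primary outcome could then pass for evidence that skill had improved.

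**Working it through.** **1. Order of events**

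| Step | Timing stated | Section |
|---|---|---|
| Oral feedback from tutor, patient and peers, on the RICS framework | immediately after each consultation | Interventions |
| Patient's MISS-21 | after each consultation, taken by an independent researcher | Primary outcome measure |
| Tutor's RICS | any time up to 24 hours after the consultation | Secondary outcome measures |

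The window allows scoring before the oral round and also after it. Nothing in the article fixes which.

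**2. When a difference between arms can arise**

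The oral round is the same in both arms and tutors do not know the arm. If patient opinion does not differ by arm, carry-over adds the same amount to both arms on average and creates no difference. A false RICS difference needs patient opinion to differ by arm, with no matching change in the skill that tutors observe.

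**3. The plan's own figure**

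Inputs from the Sample size section: 33 per group, difference 0.32, SD 0.46, 5% level (taken as two-sided), unpaired t test.

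- Standardized effect: d = 0.32 / 0.46 = 0.696. The article gives 0.69.
- Power, normal approximation: Φ(0.696 × √(33/2) − 1.96) = 80.7%.
- Power, t test: 79.5%, with a detectable difference of 0.322 at 80% power.

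The stated 80% is reproduced. The concern does not depend on it; it only supplies a scale.

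**4. Illustration of size**

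Assumptions that are not in the documents: no true effect on the RICS; the full planned MISS-21 effect of 0.696 SD; a tutor score that moves λ SD for each SD of patient satisfaction; RICS SD held at 1; students treated as independent.

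False RICS difference = λ × 0.696. Noncentrality = λ × 0.696 × √(33/2). The chance of p < 0.05 comes from the two-sided t test with 64 degrees of freedom.

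| λ | False RICS difference (SD) | Noncentrality | Chance of a significant RICS result |
|---|---|---|---|
| 0 | 0 | 0 | 5% |
| 0.1 | 0.07 | 0.28 | 5.9% |
| 0.2 | 0.14 | 0.57 | 8.6% |
| 0.3 | 0.21 | 0.85 | 13.3% |

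A simulation of 20,000 trials per value gave 5.8%, 8.4% and 13.6%.

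**5. Sensitivity to the model**

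Suppose instead that the recorded score is (1 − w) × the tutor's own view + w × the patient's opinion, both with unit variance and with correlation 0 to 0.5 between them.

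| w | False RICS difference (SD) | Chance of a significant RICS result |
|---|---|---|
| 0.1 | 0.07–0.08 | about 6% |
| 0.2 | 0.15–0.17 | 9–10% |
| 0.3 | 0.24–0.27 | 16–20% |

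Both models show little harm at low carry-over. They part at the upper end, so the figures show an order of magnitude and are not estimates.

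**The case against.** The strongest reply is that the 24 hours are an outer limit. A tutor could score first, and the order in which forms are filled in is the kind of detail that a full protocol or the tutors' standardization training may settle. This stands in part: independence is unprotected, not shown to be lost. But the article does not simply leave timing out. It states a rule, and that rule is too loose for the use the same section makes of the score.

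Second, the harmful scenario is narrow. Patients are blinded, so a large gain in their satisfaction would most likely come from changed behaviour that the tutor also sees. The tutor must also form a view on the RICS domains in time for the oral round. History taking, physical examination and problem solving are less open to an echo of satisfaction. All of this is fair and limits the likely size. It does not remove the point, because this narrow scenario is the one the RICS is said to exclude, and patient-centredness, the subscale named for analysis, is arguably the domain closest to the patient's comments.

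Third, the trial calls itself exploratory and the RICS is not powered. That is correct, and it is why the point is minor.

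A reader might infer more: that the RICS is not an independent measure, or that agreement between the two outcomes will be inflated. The documents do not support either. They do not show that tutors score after the oral round. The Objectives and hypothesis section only names tutor-reported skills as the secondary outcome and claims no independence. No analysis of agreement is planned.

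**Conclusion.** The concern holds in a limited form. The stated timing lets the tutor hear the patient's opinion before scoring, and blinding to arm does not close that route. The assurance that the RICS avoids a training effect on the MISS-21 is therefore not secured by the procedure described.

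The probability of a falsely significant RICS result would rise from 5% to about 6% to 13% for a carry-over of 0.1 to 0.3 SD per SD. This rests on an assumed carry-over, no true RICS effect and the full planned MISS-21 effect. Another equally assumed model reaches 16–20% at a weight of 0.3. The point touches one unpowered secondary outcome and is a minor improvement.

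**What to change.** In Secondary outcome measures, replace the 24-hour window with a rule such as: tutors complete and hand in the RICS at the end of the consultation, before the oral feedback round, and do not change it afterwards. Apply it at every rated session, including the first and the last, and add a line to the tutors' standardization training.

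The cost is one sentence in the protocol and an oral round that starts a few minutes later, the time needed to fill in the form. The rule itself calls for no extra staff, students or data. The Interventions section describes the oral feedback as immediate, so its wording should allow for that short delay.

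If this is not feasible, withdraw the statement that the RICS avoids a training effect on the MISS-21.

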### Implementation

An investigator (ML) generates the allocation sequence using computer-generated numbers and conceals the random sequence in sealed opaque envelopes. Another investigator (NR), not directly involved in the assessment of students, draws the envelopes and assigns participants to their study groups.

Student participants are required to complete a common assessment battery at the time of enrolment: demography, baseline RICS and MISS-21 after their first consultation. At the end of baseline assessment, student participants are randomly allocated to the RICS group (control) or combining RICS and MISS-21 (intervention).

Students in the intervention group will be able to obtain MISS-21 patient satisfaction feedback no later than one week prior to the final consultation session near the end of the semester. They are requested to complete a reflection exercise using the Pendleton model [15]. Students in the control group will be able to obtain patient feedback using the MISS-21 within one month following their final consultation session (after the intervention period). Hence, the control group will still have an opportunity for self-reflection and benefit from patient feedback to improve their consultation skills.

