### Adherence

We will recruit third-year medical students in their first clinical year to participate in the trial. This group of students is highly motivated in learning from real patient volunteers. A very high rate of retention and adherence in participation is expected.

Email adherence reminders will be sent after the participants have obtained written feedback of patient satisfaction. This reminder will emphasize the importance of following study guidelines to read the written feedback and the importance of contacting the coordinator if experiencing problems related to the study intervention. Debriefing and referral for counselling will be available to any student upon request.

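### Recording the RICS does not remove a training effect from the MISS-21 comparison, so a difference belongs to the feedback-plus-reflection package and not to the patients' ratings alone

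*Protocol article*

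**What the plan says.** The protocol article gives the MISS-21 two roles. Under Primary outcome measure: "The primary outcome measure is patient satisfaction immediately after the student consultation episodes, rated using the MISS-21". Under Interventions: "The educational intervention is written feedback using the 21-item Medical Interview Satisfaction Scale (MISS-21) in addition to the usual oral feedback". The same section describes what intervention students receive: "The intervention pack includes patient feedback questionnaires for all previous student-led consultations as well as written instructions about self-reflection on the feedback received".

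Implementation fixes the timing: "Students in the intervention group will be able to obtain MISS-21 patient satisfaction feedback no later than one week prior to the final consultation session". It adds for that arm: "They are requested to complete a reflection exercise", following the Pendleton model. Control students can obtain their MISS-21 results only in the month after their last consultation, and no reflection task is described for them before it.

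Secondary outcome measures then offers the reassurance at issue: "The concurrent use of the RICS avoids the risk of a simple training effect on MISS-21 scores".

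Objectives and hypothesis asks about written patient feedback delivered through completed MISS-21 forms and does not mention reflection. The Discussion describes the contrast as multisource feedback with or without patient satisfaction feedback.

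**The concern.** The protocol recognises a real threat and then declares it dealt with by a measure that cannot deal with it. If the teaching material is the scoring sheet, students who have studied it may score better because they know what is being scored, or because they were prompted to reflect, whatever their patients wrote. A second outcome can show whether improvement also appears elsewhere. It cannot take such an effect out of the first outcome.

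What is at stake is interpretation. If the sentence stands, a positive MISS-21 result could be reported as the effect of what patients said, with the RICS cited as having ruled out the alternative. The Discussion expects the results to inform educators and the intervention to be replicable elsewhere, so it matters which active ingredient is named.

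**Working it through.** **The plan's own figure.** Inputs from Sample size: difference 0.32, SD 0.46, 5% significance level (two-sided assumed, since sidedness is not stated), 80% power.

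n per group = 2 × (1.960 + 0.842)² × (0.46 / 0.32)² = 2 × 7.85 × 2.066 = 32.4, rounded up to 33.

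The stated 33 per group is reproduced. Power at 33 is 80.7% by the normal approximation. The exact t test gives 33.4 per group and 79.5% power at 33. The calculation concerns the MISS-21 only, and nothing in it depends on the disputed sentence. The remaining question is one of attribution, so the sections are set side by side.

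**What each arm has before the final rating**

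| Element | Intervention | Control | Section |
|---|---|---|---|
| Oral feedback from tutor, patient and peers | yes | yes | Interventions |
| That oral feedback follows the RICS framework | yes | yes | Interventions |
| Completed MISS-21 forms, hence the 21 items | yes | not given until after the last session | Interventions, Implementation |
| Guided reflection task | requested | none described | Interventions, Implementation |

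**What the MISS-21 contrast contains.** As a simple additive description, write the between-arm difference as D = a + b + c, where a is due to the content of the patients' ratings, b to familiarity with the scored items and c to guided reflection. The trial estimates D. It has one contrast for three unknowns, so a cannot be isolated.

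**What the RICS adds.** The RICS contrast is a second quantity, D′ = a′ + b′ + c′, with its own three unknowns on another scale and from another rater. Observing D′ leaves b and c inside D. Recording the RICS also changes no row of the table.

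**How strong the RICS is as corroboration.** It is scored by blinded tutors and is not the questionnaire handed out, so a gain on both instruments would count against pure item-learning. Three features limit this:

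- Sample size says that the RICS was not used in the power calculation.
- Data management and statistical methods names only its patient-centeredness subscale as a dependent variable.
- The article gives no rule for reading a MISS-21 gain that is not matched by a RICS gain.

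**The case against.** The strongest reply is that the package is the intervention. The hypothesis names completed MISS-21 forms as the vehicle of feedback, so seeing the items is part of what is tested. Interventions openly lists the "written instructions about self-reflection on the feedback received". Students are randomized, and patients, tutors and analysts are blinded. The article calls the trial exploratory, and comparing an educational package with usual teaching is a legitimate design. All of this stands. A reader might infer from the shared instrument that a difference could not be credited to the intervention at all, or that the trial cannot answer its question. The document does not support that: the effect of the package is identified, and the protocol does not promise to separate its parts.

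A second reply reads the disputed sentence charitably: a different instrument with different raters guards against relying on a gain confined to the MISS-21. That is a fair account of what the RICS can contribute, but it describes exploring a risk, whereas the sentence claims to avoid it.

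A third reply is that Implementation lists a baseline MISS-21 for all students, so controls might know the form. However, Primary outcome measure says that an independent researcher obtains the scores by interviewing the patient. Nothing says that students are shown the form at baseline.

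A reader might also infer that controls should receive a blank form and the same reflection task. That would replace the stated comparator, usual oral feedback alone, with a more active one, and would test a narrower contrast than the one the sample size was planned for. It is a debatable trade-off, and correcting the error does not require it.

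**Conclusion.** The sentence claims a property that the design lacks and should not stand. A MISS-21 difference between arms supports a conclusion about written MISS-21 feedback combined with guided reflection. It does not support a conclusion about the content of the patients' ratings alone, and the RICS does not change that.

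No size can be attached: the article gives no information on how far item familiarity or reflection moves MISS-21 scores, and any split of the planned 0.32 points would be guesswork. The sample size is unaffected.

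The conclusion rests on two readings of the text: that controls are not given the MISS-21 form before their final rating, and that they have no equivalent reflection task in that period. If controls in fact had either, the corresponding part of the arm difference would shrink, but the sentence about the RICS would still be wrong.

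**What to change.** 1. In Secondary outcome measures, replace the sentence with a statement that the RICS helps to explore whether a MISS-21 gain generalises beyond the items students have seen. Add that a MISS-21 gain without a RICS gain will be reported as compatible with a training effect. Because the trial was not powered on the RICS, the absence of a RICS gain should not be presented as proof of one.
2. In Objectives and hypothesis and in the Discussion, name the intervention as written MISS-21 feedback plus guided reflection, and limit conclusions to that package.

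Both changes are wording only. They leave the design, comparator, sample size and data collection as they are. The only cost is a narrower claim.
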